**Primary outcomes**

Disability was assessed with the Roland Morris Disability Questionnaire (RMDQ), which contains 24 items that are closely related to the daily life activities of patients with CLBP.(Mbada et al., 2017) The scores are as follows: 1 for checking ‘YES’ and 0 for checking ‘NO’. The final score varies from 0 to 24. Higher scores are associated with more severe disability.(Yi et al., 2012)

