
10. The participants’ overall assessment of the treatment was measured on the basis of the global perceived effect (GPE). The GPE scale requires patients to rate how much they have improved or deteriorated since they received the treatment. The use of this scale is widely advocated in pain research because it is easy and quick to understand and score, and its results are important to patients.(Evans, Bronfort, Maiers, Schulz, & Hartvigsen, 2014) The most meaningful changes can be observed in patients answering the scale at a predefined time point. The GPE scale has excellent reproducibility (ICC = 0.90–0.99), and its correlation with disability (r = 0.40–0.74) is strong.(Kamper et al., 2010)

11. Adverse events were collected from participants’ daily record forms. All pain (LBP or other pain) related to intervention or unrelated to intervention occurring during the research duration was considered.

12. The participants’ recommendation levels on the intervention that they received were classified as highly recommended, recommend, unclear, not recommended and strongly deprecated.

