**Sample size calculation**

Sample size was calculated by G*power 3.1.9 based on the following conditions. According to Costantino's trial, the subjects of the two groups received 12 weeks of aquatic exercise and back school program respectively. The effect size was calculated to be 0.35 by using the RMDQ score of the experimental group (mean = 5.37, SD = 1.82) and the control group (mean = 6.11, SD = 2.36) during the 3-month follow-up.(Costantino & Romiti, 2014) The two groups were measured 4 times by using a mixed design of repeated measures analysis of variance. Considering that α = 0.05, power (1-β) = 0.95, Corr amongst rep measures = 0.5, the total sample size was 70. Considering the possibility of a 20% missing rate, the minimum sample size was 88. According to the calculation, 100 subjects will be expected to be recruited, and 50 subjects will be included in each group.

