**Statistical analysis**

Data will be collected and analyzed via SPSS 20.0 and Microsoft 2016. Considering that someone may drop out midway, all outcomes should be conducted by intention-to-treat analysis and per-protocol analysis. For baseline variables, we will detect the categorical variables (e.g. gender, education levels and occupation) with chi-square test and analyze the continuous variables (e.g. age, height, weight, BMI, and pain intensity) with independent t-test or Mann–Whitney U test to compare the statistical significance between the TAE group and the PTMs group. The results of descriptive statistics will be presented as mean ± standard deviation.

The experimental results were compared through adjusted two-way repeated measures ANOVA (group × time). The adjustment factors included gender, age, BMI, physical activity, LBP duration, NRS of the most severe LBP, medication, and smoking history. A chi-square test was conducted to compare the proportion of participants in each group who met the MCID for pain and function at postintervention. Although the MCID for RMDQ and NRS remains controversial, values of 5.0 and 2.0 are considered reasonable and commonly used. The χ2 test was also applied to determine the difference between the 2 groups for the proportion of participants reporting GPE, adverse events and treatment recommendations. The effect sizes were presented to measure the strength of any outcome indicators, where 0.2 ≤ Cohen’s d < 0.5 means a ‘small’ effect size, 0.5 ≤ Cohen’s d < 0.8 indicates a ‘medium’ effect size and Cohen’s d ≥ 0.8 reflects a ‘large’ effect size.

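### The χ² test named for GPE and treatment recommendation ignores the order of the response levels and is less efficient than an ordinal test against a one-directional benefit; low severity, secondary outcomes only

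*Protocol*

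**What the plan says.** The last paragraph of the protocol's Statistical analysis section assigns a χ² test to the share of participants in each arm who reach the MCID for pain and function. It then extends the same method to further outcomes with the words "test was also applied to determine the difference between the 2 groups for the proportion of participants reporting GPE, adverse events and treatment recommendations". No rank test, trend test or ordinal model is named for these items.

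Secondary outcomes, item 12, says that recommendation levels "were classified as highly recommended, recommend, unclear, not recommended and strongly deprecated". Item 10 describes GPE in these words: "The GPE scale requires patients to rate how much they have improved or deteriorated since they received the treatment". It gives neither the number of GPE levels nor a cut-point. Table 3 schedules both at 3, 6 and 12 months.

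A rank test already appears in the plan, but only for baseline comparisons of continuous variables, made "with independent t-test or Mann–Whitney U test to compare the statistical significance between the TAE group and the PTMs group". The hypothesis for Aim 1 (Research goals and hypotheses) is directional: more benefit in pain and function under TAE than under PTMs. RMDQ is the only primary outcome.

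**The concern.** Both scales have a natural order. A Pearson χ² test on a 2 × 5 table has 4 degrees of freedom and gives the same result if the five levels are shuffled. If TAE moves answers towards the favourable end, as the trial's hypothesis suggests, a test that uses the order puts its power on that shift. The χ² test spreads its power over every way in which the two distributions could differ.

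At stake are the patients' own verdicts on treatment. A moderate real shift is more likely to be reported as non-significant than it need be.

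**Working it through.** **Inputs from the protocol.** α = 0.05 (taken as two-sided). Planned enrolment is 50 per arm; the protocol's 20% missing rate would leave 50 × 0.8 = 40. The protocol states no power for GPE or recommendation, so there is no figure of its own to reproduce here. Its sample size concerns RMDQ.

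**Assumptions (not in the documents).** The response distribution, the common odds ratio, and proportional odds.

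**One case by hand.** Take PTM responses of 20/40/25/10/5%, a common OR of 2, and n = 50 per arm.

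- PTM cumulative proportions are 0.20, 0.60, 0.85, 0.95, with odds 0.25, 1.5, 5.667, 19. Doubling the odds gives TAE cumulative proportions 0.3333, 0.75, 0.9189, 0.9744, so the TAE levels are 0.3333, 0.4167, 0.1689, 0.0554, 0.0256.
- χ² on all levels: λ = n Σ (pⱼ − qⱼ)²/(pⱼ + qⱼ) = 50 × (0.0333 + 0.0003 + 0.0157 + 0.0128 + 0.0078) = 3.50. On 4 df (critical value 9.49), power is 0.28.
- Rank test: with p̄ⱼ the average of the two arms, Σ p̄ⱼ³ = 0.0968. Then z = ln 2 × √[50 × (1 − 0.0968)/6] = 0.693 × 2.744 = 1.902, and power = Φ(1.902 − 1.960) = 0.48.
- 2 × 2 χ² on the top two levels, 0.60 against 0.75: λ = 50 × 0.15²/1.35 + 50 × 0.15²/0.65 = 0.833 + 1.731 = 2.56. On 1 df, power is 0.36.

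The loss is about 20 points on the full table and about 12 on the two-category comparison. Simulation of this case gives 0.26 for the full-table χ² and 0.46 for Mann–Whitney, close to the approximations.

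**Range.** Simulation, 20,000 trials per setting, five levels, 50 per arm, four assumed shapes (uniform, bell, skewed, strongly skewed):

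| Common OR | χ², all levels | Rank test | Loss (points) |
|---|---|---|---|
| 1.5 | 0.10–0.12 | 0.20 | 8–9 |
| 2 | 0.26–0.29 | 0.46–0.49 | 20 |
| 2.5 | 0.44–0.50 | 0.68–0.72 | 22–24 |
| 3 | 0.62–0.66 | 0.83–0.86 | 20–21 |
| 4 | 0.84–0.87 | 0.95–0.97 | 10–11 |
| 6 | 0.97–0.98 | 1.00 | 1–3 |

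With 40 per arm the loss is 17–24 points at OR 2–3 and 15–18 at OR 4. If GPE had seven levels (an assumption), the loss with 50 per arm would be 25–32 points at OR 2–3.

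**Two-category reading.** At the best cut the loss is about 6–15 points at OR 2–3 with 50 per arm; a poor cut loses more.

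**Validity.** With 50 per arm and no true difference, the χ² test rejected in 0.038–0.048 of simulated trials, so no inflation is seen. The share of trials in which more than 20% of expected counts fell below 5 was 0–3% (uniform), 6–19% (bell), 43–88% (skewed) and 75–84% (strongly skewed).

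**Differences without a direction.** In two settings where one arm had more answers at both ends of the scale, χ² power was 0.52 and 0.54, against 0.05 and 0.07 for the rank test.

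**The case against.** The strongest reply is that the protocol speaks of proportions of participants, directly after using χ² for the yes/no MCID outcomes. GPE and recommendation may therefore be meant as two-category comparisons, such as improved or not. The test would then have 1 degree of freedom and the percentages would show the direction. This reading is open, and the cut-point may stand in a statistical analysis plan that is not shown. It reduces the loss but does not remove it.

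The reply is also right that this is a matter of efficiency and not an error, that no power is claimed for these outcomes, and that proportional odds is the setting that favours a rank test.

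Four stronger readings are tempting, and the documents do not support them:

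- A reader might infer a fixed loss of about 20 points. That holds only for moderate one-directional shifts under assumed distributions.
- A reader might infer that sparse cells make the χ² test unreliable. Sparsity depends on how skewed the answers are, which the protocol does not say, and no type I inflation appeared.
- A reader might infer that χ² brings no benefit. It is clearly better for differences without a direction.
- A reader might extend the point to adverse events and ask for an exact test. No event rate is given, and χ² suits a yes/no comparison with adequate counts.

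**Conclusion.** The point holds as a low-severity matter of efficiency. The protocol names a test that does not use order for two ordered scales, while its hypothesis has a direction. That hypothesis is worded for pain and function; carrying the direction over to GPE and recommendation is a reasonable inference, not a statement in the text.

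With five levels and 50 per arm, the loss runs from 1 to 24 points over odds ratios of 1.5 to 6 and is greatest between 2 and 3. Every figure rests on assumed distributions and proportional odds. Five levels are documented for recommendation only. The planned test is valid, and the primary RMDQ analysis is untouched.

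**What to change.** Replace the χ² test for GPE and recommendation with a Mann–Whitney test, or with a proportional-odds model reporting a common odds ratio and 95% CI, at 3, 6 and 12 months. Show the percentage in each category by arm as description. Keep χ² for adverse events analysed as yes/no. If a two-category comparison of either scale is intended, say so and fix the cut-point before the data are seen.

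The cost is one sentence of analysis wording. Both methods are available in SPSS 20.0, which the protocol names, and Mann–Whitney is already in the plan for baseline variables. The one small downside is lower sensitivity to differences without a direction; the category percentages would still let a reader see such a pattern.

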**Discussion**

With various properties of water, TAE should be an acceptable and effective treatment for CLBP. In TAE usually performed in a group, creating high compliance and great effects on pain, people with CLBP interact with others with similar problems and receive peer support.(Buchbinder et al., 2018; Lamb et al., 2010; Qaseem et al., 2017) TAE is a proactive and enjoyable treatment to convey the positive health concept naturally,(Huber et al., 2016) which will cause long-term effects by avoiding unhealthy behaviors, such as absence from work and prolonged rest.(Auvinen, Tammelin, Taimela, Zitting, & Karppinen, 2008; Buchbinder et al., 2018) Compared to PTMs, TAE can be carried out by patients themselves, which will cut down the medical expenditure to some extent.

To the best of our knowledge, this work is the first to compare the effect between TAE and PTMs on patients with CLBP. Thus, our study may also have the potential to optimize the strength of the water exercise, and our findings may provide broad functional and psychological benefits to practical applications.

**Strengths and limitations**

First, the research duration of most previous studies typically ranged from several weeks to 2 months.(Backhausen et al., 2017; Barker et al., 2016; Lambert et al., 2014; Nguyen et al., 2017; Smith & Lyle, 2006) This study will include an intervention period of 3 months and a follow-up period (without intervention) of 3 and 9 months, making the entire term of 1 year. Second, our study will offer the same attention to all participants by designing the two programs with equal time, thereby reducing other biases compared with former studies.(Koes, 2011) Third, we will add some psychological scales and lifestyle-related issues into our measurement. Thus, the CLBP will be accessed in a multi-tiered system.

Nevertheless, this method is not the perfect protocol. On the one hand, recall bias in questionnaire responses is inevitable, but we do not have enough data to show this influence. On the other hand, included people may have CLBP with different durations and degrees. Controlling the disease progression that affects individual physical fitness is difficult.

In conclusion, this trial aims to investigate the effect of TAE on people with CLBP and determine whether TAE elicits better results than PTMs. Our findings will provide patients with an enjoyable and effective way to recovery, lessen the medical burden of CLBP, and change the public health and prevention strategies worldwide.(Koes, 2011; Silvers, Rutledge, & Dolny, 2007)

| Dynamic drafting | 4min, continuously  30 s × 8 parts | Stretching the muscles of the neck, shoulder, back, hip, knee, and ankle slowly and repeatedly to increase the range of motion of the entire joint. | Increase speed | [figure not shown] | / |
| Pool walking | 4 min, continuously | Walking in the water with tightening abdomen and straight back, and the heel touchdown before the front foot. | Increase speed | [figure not shown] | / |
| High leg kicks | 1 min, continuously | Raising the legs alternately with fast rhythm. The body should be in the same position, and the upper body is upright. The heel of the supporting leg must be off the ground. | Increase speed | [figure not shown] | / |
| Jumping jacks | 1 min, continuously | Standing in chest-level water with your feet together and your arms by your side. Jumping with two legs outward and arms lifted up to the head simultaneously, then bring the two legs together and put down the arms back to your side. | Increase speed | [figure not shown] | / |
| Core exercise (40 min) | | | | | |
| Abdominal bracing | 5 min  15 s × 20reps  Maintain 10 s, rest 5 s | Standing still with your back in a relaxed neutral spine position, gently contracting your abdominal muscles to move the rib toward the hip and the navel to the spine. | Increase maintenance time | [figure not shown] | / |
| Vertical downward press | 5 min  15 s × 20 reps  Maintain 10 s, rest 5 s | Standing upright with feet shoulder-width apart and toes forward, pressing the dumbbell vertical downward against the water with two hands. Then, the dumbbell was allowed to return to the surface slowly | Increase maintenance time, resistance | [figure not shown] | Dumbbell、kickboard |
| Lateral downward press | 5min  15 s × 20 reps  Maintain 10 s, rest 5 s | Standing upright with the feet shoulder-width apart and toes forward, pressing the kickboard lateral downward against the water with the two hands. | Increase maintenance time, resistance | [figure not shown] | Dumbbell, kickboard |
| Slant downward press | 10min  30 s × 20 reps×2direction  Maintain20 s, rest 10 s | Standing upright with feet shoulder-width apart and toes forward, holding the dumbbell with two hands in the direction of one shoulder, then pressing it slant downward against the water to the hip in another side. | Increase speed and repetitions | [figure not shown] | Dumbbell, kickboard |
| Straight leg pressing | 5 min  30 s × 20 reps  Maintain20 s, rest 10 s | Standing with your back to the side of the pool in chest-high water, placing your arms on the edge of the pool for stability. Raising your two legs up together with straight knee joint, then return to standing position with two legs pressing against water. | Increase speed and repetitions, resistance | [figure not shown] | Dumbbell, kickboard |
| Water treading | 5 mins  30 s × 20 reps  Maintain 20 s, rest 10 s | Standing in chin-high water with your feet held stationary on the top of a kickboard, paddle your arms to keep balance and kick your legs as your lower body rises off the ground and your knees to the chest. Then, extend your hips and knees fully to push the board reach the floor | Increase speed, maintain time | [figure not shown] | kickboard |
| Deep water running | 5 min  Continuously run 50–100 m | A swim belt is needed to perform the exercise. Keep your body straight up in the water with your shoulders back and your head and eyes looking at the horizon. Pull your knees up as high as hip height, and slightly point your toes. Swing your arms with reciprocal boxing movements. The body will be propelled slowly forward | Increase speed and running mileage | [figure not shown] | Swim belt |
| Cool-down (10min) | | | | | |
| Static stretching | 5 min  20 s × 3 reps × 5 parts  Maintain 15 s, rest 5 s | Slowly lengthen the muscles of the shoulders, back, abdomen, and thighs, shins respectively, and keep them in a comfortable position for 15–20 s. | / | [figure not shown] | / |
| Back float | 3 min  Continuously | Wearing a swim belt, lie as parallel to the ground as possible according to the instructions of the experimenter. Assistance given by the experimenter will be reduced gradually, and finally stop the assistance. | Decrease assistance | [figure not shown] | Swim belt, kickboard |

Table 2 demographics and baseline characteristics of all participants

| **Characteristic** | **therapeutic aquatic exercise** | **physical therapy modalities** |
| --- | --- | --- |
| Mean age (SD), y | ✖ | ✖ |
| Sex-female, N (%) | ✖ | ✖ |
| Mean height (SD), m | ✖ | ✖ |
| Mean weight (SD), kg | ✖ | ✖ |
| Mean BMI(SD), kg/m2 | ✖ | ✖ |
| **Education levels** |  |  |
| Illiteracy, N (%) | ✖ | ✖ |
| Primary school, N (%) | ✖ | ✖ |
| Junior middle school, N (%) | ✖ | ✖ |
| High school, N (%) | ✖ | ✖ |
| University, N (%) | ✖ | ✖ |
| Postgraduate, N (%) | ✖ | ✖ |
| **Employment status** |  |  |
| Employed part-time, No. (%) | ✖ | ✖ |
| Employed full-time, No. (%) | ✖ | ✖ |
| Unemployed, No. (%) | ✖ | ✖ |
| Not trying to look for employment, No. (%) | ✖ | ✖ |
| Unable to work due to poor health, No. (%) |  |  |
| Student, No. (%) | ✖ | ✖ |
| Retired, No. (%) | ✖ | ✖ |
| **Personal monthly income, yuan** | ✖ | ✖ |
| ≥10000, No. (%) | ✖ | ✖ |
| 5000-10000, No. (%) |  |  |
| 3000-5000, No. (%) | ✖ | ✖ |
| ＜3000, No. (%) | ✖ | ✖ |
| Refused, No. (%) | ✖ | ✖ |
| **Smoking history** |  |  |
| Smoking, No. (%) |  |  |
| Years of smoking, mean (SD), y | ✖ | ✖ |
| Smoking per day, mean (SD) | ✖ | ✖ |
| Low back pain duration, mean (SD), y | ✖ | ✖ |
| Duration of first onset, mean (SD),d | ✖ | ✖ |
| **Current back pain intensity** |  |  |
| Most serious pain in previous week, mean NRS score (SD) | ✖ | ✖ |
| Slightest pain in previous week, mean NRS score (SD) | ✖ | ✖ |
| Average pain in previous week, mean NRS score (SD) | ✖ | ✖ |
| Current pain intensity, mean NRS score (SD) | ✖ | ✖ |
| Work absence or reduced hours, mean (SD), h | ✖ | ✖ |
| Medical expenditure on back pain last year, mean (SD), yuan | ✖ | ✖ |
| **Medication use in previous three months** |  |  |
| No medication, No. (%) | ✖ | ✖ |
| Pain reliever, No. (%) | ✖ | ✖ |
| Adjuvant drugs, No. (%) | ✖ | ✖ |
| Drugs for other disease, No. (%) | ✖ | ✖ |
| **Belief that invention works** |  |  |
| Yes, No. (%) | ✖ | ✖ |
| No, No. (%) | ✖ | ✖ |
| Don't know, No. (%) | ✖ | ✖ |
| **Expectation that invention works** |  |  |
| Yes, No. (%) | ✖ | ✖ |
| No, No. (%) | ✖ | ✖ |
| Don't know, No. (%) | ✖ | ✖ |
| **Marital status** |  |  |
| Unmarried, No. (%) | ✖ | ✖ |
| Married, No. (%) | ✖ | ✖ |
| Divorced, No. (%) | ✖ | ✖ |
| Widowhood, No. (%) | ✖ | ✖ |
| **Occupation** |  |  |
| Sitting time , mean (SD), h | ✖ | ✖ |
| Standing time, mean (SD), h | ✖ | ✖ |
| Others, mean (SD), h | ✖ | ✖ |
| **Physical activity** |  |  |
| **High intensity physical activity per week** |  |  |
| ＜150min per day, No. (%) | ✖ | ✖ |
| 150-300min per day, No. (%) | ✖ | ✖ |
| ＞300min per day, No. (%) | ✖ | ✖ |
| **Moderate intensity physical activity per week** |  |  |
| ＜75min per day, No. (%) | ✖ | ✖ |
| 75-150min per day, No. (%) | ✖ | ✖ |
| ＞150min per day, No. (%) | ✖ | ✖ |
| **Cause of first onset** |  |  |
| Hyperactivity or improper exercise, No. (%) | ✖ | ✖ |
| Sedentary lifestyle, No. (%) | ✖ | ✖ |
| Pregnancy, No. (%) | ✖ | ✖ |
| Others, No. (%) | ✖ | ✖ |
| **Site of first onset** |  |  |
| Left, No. (%) | ✖ | ✖ |
| Right, No. (%) | ✖ | ✖ |
| Middle, No. (%) | ✖ | ✖ |
| Both two sides, No. (%) | ✖ | ✖ |
| Others, No. (%) | ✖ | ✖ |
| **Site of current LBP** |  |  |
| Left, No. (%) | ✖ | ✖ |
| Right, No. (%) | ✖ | ✖ |
| Middle, No. (%) | ✖ | ✖ |
| Both two sides, No. (%) | ✖ | ✖ |
| Others, No. (%) | ✖ | ✖ |
| Duration of the latest low back pain, mean (SD),d | ✖ | ✖ |
| Frequency of low back pain last month, mean (SD) | ✖ | ✖ |
| Duration of low back pain per day last week, mean (SD),h | ✖ | ✖ |
| **Influence of low back pain on work** |  |  |
| Free, No. (%) | ✖ | ✖ |
| mild, No. (%) | ✖ | ✖ |
| moderate, No. (%) | ✖ | ✖ |
| severe, No. (%) | ✖ | ✖ |
| **Influence of low back pain on life** |  |  |
| Free, No. (%) | ✖ | ✖ |
| mild, No. (%) | ✖ | ✖ |
| moderate, No. (%) | ✖ | ✖ |
| severe, No. (%) | ✖ | ✖ |
| **Pain mode in 24-hour** |  |  |
| gradually aggravate, No. (%) | ✖ | ✖ |
| gradually relieve, No. (%) | ✖ | ✖ |
| no change, No. (%) | ✖ | ✖ |
| Others, No. (%) | ✖ | ✖ |
| **Factors aggravating low back pain** |  |  |
| Sitting, No. (%) | ✖ | ✖ |
| Standing, No. (%) | ✖ | ✖ |
| Walking, No. (%) | ✖ | ✖ |
| Bending, No. (%) | ✖ | ✖ |
| Squat down, No. (%) | ✖ | ✖ |
| Go upstairs, No. (%) | ✖ | ✖ |
| Go downstairs, No. (%) | ✖ | ✖ |
| Postural change, No. (%) | ✖ | ✖ |
| Others, No. (%) | ✖ | ✖ |
| **Factors to relieve low back pain** |  |  |
| Recumbent rest, No. (%) | ✖ | ✖ |
| Sitting for rest, No. (%) | ✖ | ✖ |
| Small intensity activities, No. (%) | ✖ | ✖ |
| Others, No. (%) | ✖ | ✖ |
| **Nature of pain** |  |  |
| Soreness, No. (%) | ✖ | ✖ |
| Distended pain, No. (%) | ✖ | ✖ |
| Radiation pain, No. (%) | ✖ | ✖ |
| Burning pain, No. (%) | ✖ | ✖ |
| Needling pain, No. (%) | ✖ | ✖ |
| Other, No. (%) | ✖ | ✖ |

SD= Standard Deviation, BMI=Body Mass Index, VAS= Visual Analogue Scale, RMDQ= Roland Morris Disability Questionnaire

Table 3 Outline of measurement time points

|  | Baseline | 3 months | 6 months | 12 months |
| --- | --- | --- | --- | --- |
| Numeric rating scale (NRS) | ✖ | ✖ | ✖ | ✖ |
| Roland Morris Disability Questionnaire (RMDQ) | ✖ | ✖ | ✖ | ✖ |
| the Short Form (36) Health Survey | ✖ | ✖ | ✖ | ✖ |
| Self-Rating Anxiety Scale (SAS) | ✖ | ✖ | ✖ | ✖ |
| Zung Self-Rating Depression Scale (SDS) | ✖ | ✖ | ✖ | ✖ |
| Pittsburgh Sleep Quality Index (PSQI) | ✖ | ✖ | ✖ | ✖ |
| The Pain Anxiety Symptoms Scale (PASS) | ✖ | ✖ | ✖ | ✖ |
| Tampa Scale for Kinesiophobia (TSK) | ✖ | ✖ | ✖ | ✖ |
| Fear Avoidance Beliefs Questionnaire (FABQ) | ✖ | ✖ | ✖ | ✖ |
| The Minimal Clinically Important Difference (MCID) |  | ✖ | ✖ | ✖ |
| Global Perceived Effect (GPE) |  | ✖ | ✖ | ✖ |
| Adverse Events |  | ✖ | ✖ | ✖ |
| Recommendation |  | ✖ | ✖ | ✖ |

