**TAE group**

The temperature will be customized at 30 °C of water and 27.5 °C of environment to elicit the same heart response both in water and in air. The entire intervention will be completed in a swimming pool with a dimension of 20 m × 6 m and a depth of 1.3–1.5 m. To ensure that all of the participants will be submerged at their xiphoid bone level, some aquatic steps will be placed underwater as auxiliary forces.

The TAE protocol will be designed by the researcher in accordance with available scientific evidence. During the exercise, the participants will receive verbal, tactile, and visual information to correct their movements and ensure that the lumbar spine remains in a neutral position while standing. Thus, excessive loading on the spine will be avoided, and trunk muscles will be activated. The target exercise intensity will depend on the subject’s self-rated score of Rating of Perceived Exertion of approximately 13 in accordance with 60%–80% of maximum heart rate.(Wallace, Slattery, & Coutts, 2009)

The participants will start the exercise with an active warm-up for 10min to enhance neuromuscular activation. In the succeeding 40 min, they will perform an aquatic session, including abdominal bracing, vertical downward press, lateral downward press, slant downward press, straight leg raising, treading water, and deep water running. Finally, the participants will have a cool-down period for 10min. Table 1 shows the full description of the protocol.

All subjects will participate in the exercise in a group of 8–9 people. Weeks 1 and 2 are the learning period for subjects to become familiar with the actions. Then, the intensity of movements will be adjusted by changing the kickboard sizes. Thus, the neuromuscular stimulation will be maximized, and the subjects’ interest will also be maintained.

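### In Table 1, three core exercises carry repetition counts that take twice the minutes in the same cell, so the 40-minute core and the equal-time design hold only if the minutes are followed

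*Protocol*

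**What the plan says.** The TAE group section describes a session in three parts: an "active warm-up for 10min", a core block ("In the succeeding 40 min, they will perform an aquatic session") and a 10-min cool-down. It points to Table 1 as the complete description of the programme. The Table 1 heading repeats the core length: "Core exercise (40 min". Each exercise row then gives minutes and, in most cases, a prescription of seconds per repetition times number of repetitions.

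For the slant downward press the cell gives 10 min and "30 s × 20 reps×2direction", with the cycle spelled out as "Maintain20 s, rest 10 s". Straight leg pressing and water treading each give 5 min and 20 repetitions of 30 s, with the same hold and rest.

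The PTMs group section gives two modalities of 30 min each. The Interventions section gives both arms 24 sessions. Under Strengths and limitations the Protocol states that "our study will offer the same attention to all participants by designing the two programs with equal time", and presents this as reducing bias.

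**The concern.** Three of the seven core rows contain two figures that cannot both be followed. Table 1 is the working description of the experimental intervention, so an instructor must choose between the clock and the count. Following the clock delivers half the written repetitions in those rows. Following the count makes the session longer than the text says.

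The second consequence touches a stated design safeguard. Participants know their allocation, and the primary outcome, the Roland Morris Disability Questionnaire, is self-reported, so the Protocol has good reason to equalise contact time. Whether it does so depends on which figure in these cells is used. The daily record form described under Interventions lists attendance, medication changes and adverse events. It does not list session length, so a departure might not be noticed.

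**Working it through.** **Inputs.** Minutes, seconds and repetitions are from Table 1. The 10 + 40 + 10 min session structure is from the TAE group section, the two 30-min modalities are from the PTMs group section, and the 24 sessions are from Interventions.

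**Formula.** Row duration in minutes = seconds per repetition × repetitions (× directions or parts) / 60.

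**Core rows.**

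| Exercise | Minutes stated | From the repetitions |
| --- | --- | --- |
| Abdominal bracing | 5 | 15 × 20 / 60 = 5 |
| Vertical downward press | 5 | 15 × 20 / 60 = 5 |
| Lateral downward press | 5 | 15 × 20 / 60 = 5 |
| Slant downward press | 10 | 30 × 20 × 2 / 60 = 20 |
| Straight leg pressing | 5 | 30 × 20 / 60 = 10 |
| Water treading | 5 | 30 × 20 / 60 = 10 |
| Deep water running | 5 | no count ("Continuously run 50–100 m"); 5 min taken as stated |
| **Total** | **40** | **60** |

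The minutes column reproduces the 40-min core. The repetitions do not: the excess is 10 + 5 + 5 = 20 min.

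**Is the notation being misread?** Every other row that gives both minutes and a count agrees with itself. The three 15-s rows give 5 min each. The first warm-up row gives 30 × 8 / 60 = 4 min. Static stretching, "20 s × 3 reps × 5 parts", gives 20 × 3 × 5 / 60 = 5 min. The warm-up items add to 4 + 4 + 1 + 1 = 10 min, as stated.

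**Does rest time explain the gap?** No. In all three rows 20 s hold + 10 s rest = 30 s, so rest is already inside the 30-s cycle.

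**Is there a more lenient reading of the slant row?** If the 20 repetitions are the total over both directions, the row takes 30 × 20 / 60 = 10 min and agrees with its minutes. The core is then 5 + 5 + 5 + 10 + 10 + 10 + 5 = 50 min, still not 40, because the other two rows remain doubled.

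**Cool-down.** The listed items are 5 + 3 = 8 min against the stated 10 min.

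**Session length.**

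- By the minutes: 10 + 40 + 10 = 60 min.
- By the repetitions, upper end: 10 + 60 + 10 = 80 min (78 min with the 8-min cool-down).
- By the repetitions, lower end: 10 + 50 + 8 = 68 min (70 min with the 10-min cool-down).
- PTMs: 30 + 30 = 60 min if the modalities are consecutive.

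**Over 24 sessions.** TAE by the repetitions: 24 × 68 / 60 = 27.2 h to 24 × 80 / 60 = 32 h. PTMs, and TAE by the minutes: 24 × 60 / 60 = 24 h. The excess is 3.2 to 8 h per participant.

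**The case against.** The strongest reply is that every explicit statement of duration agrees. The seven core entries add to 40, the table heading and the text both say 40, the session is 60 min, and PTMs is 30 + 30 min. The equal-time sentence is about how the programmes were designed, and on stated durations it is correct. This stands. A reader might infer that the equal-time claim is false, or that TAE participants will receive a third more contact time. The Protocol supports neither: equal time is lost only if instructors work to the repetition counts.

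A reader might also infer that dose will differ from class to class. That is possible, since the cells allow either choice, but nothing in the Protocol shows that it will happen. Delivered repetitions are also meant to change over the programme: the slant and straight-leg rows list more repetitions as a progression, and intensity is guided by perceived exertion and kickboard size. This weakens the step from an inconsistent table to uncontrolled dose. It does not reconcile the starting prescription, which is what the progression builds on.

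The 80-min session is the upper end of a range and should not be quoted alone. The 60-min comparator is an assumption, because the PTMs group section does not say whether the modalities are given in sequence. The equal-time statement fits that reading, but the text does not spell it out.

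Finally, one might argue from this point that attention is unequal because TAE is coached in groups and PTMs is received passively. That concerns the kind of attention, and this arithmetic says nothing about it.

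**Conclusion.** The internal contradiction is certain on the Protocol's own figures. Two rows (straight leg pressing and water treading) are doubled on any reading. The slant row is doubled if its direction multiplier is taken as written. The core takes 60 min by the repetitions, or 50 min on the lenient slant reading, against 40 min stated.

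The effect on equal time is conditional. By the repetitions, TAE runs 8 to 20 min per session longer than a 60-min PTMs session. By the minutes, the arms match, and the affected exercises get half the written repetitions (two exercises instead of three on the lenient slant reading). These figures assume consecutive PTMs modalities and deep water running at its stated 5 min.

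The point matters for reproducibility of the experimental intervention and for one stated safeguard against bias. It does not touch the endpoint, the sample size or the analysis. It should be corrected because the correction is cheap and settles what is delivered. Which figure is right is for the sponsor to decide and is not judged here.

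**What to change.** Before the first class, reconcile the minutes and repetitions in the slant downward press, straight leg pressing and water treading rows of Table 1 with each other, with the 40-min core in the TAE group section, and with the equal-time statement under Strengths and limitations. State whether the slant repetitions are per direction or in total. Reconcile the cool-down items (8 min) with the stated 10 min at the same time.

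Optionally, add delivered session minutes to the existing daily record form in both arms, so that equal contact time can be shown and not only planned.

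The cost is a correction to one table, a check of one sentence and, if the option is taken, one extra field on a form already in use.
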